## Abstract

**Background:**

Aggression, substance use, and gambling behaviour often co-occur in a larger pattern of dysregulated behaviour. One of the factors that may underlie this phenomenon is impaired inhibitory control. Inhibitory Control Training (ICT) is an alternative intervention being tested for addressing addictive behaviours by targeting inhibitory control. Given the shared underlying mechanisms of these behaviours, applying ICT to aggression represents a possible extension of this intervention. This research will mark the first implementation of a cognitive bias modification approach to managing aggression among patients with co-occurring substance use disorder and gambling behaviour in the Indian context. A secondary aim of this study will be to assess whether changes in aggression and inhibitory control will be associated with reductions in substance use disorder and gambling behaviour.

**Methods:**

A two-group, parallel randomized controlled trial will be carried out in 130 male in-patients at a tertiary care centre. Participants fulfilling the DSM-5 criteria for substance use disorders, and screening positive for problem (Score ≥ 1) or pathological (Score ≥ 5) gambling on the South Oaks Gambling Screen will be randomly allocated to either experimental (ICT) or control (Sham Training) group. The ICT consists of six 15-min sessions over three days, using a Go/No-Go paradigm with 100% contingency. ST is matched with the active training in terms of both stimulus exposure and response requirements, but reduces the contingency agreement to 50%, thereby preventing the formation of associations between aggressive stimuli and inhibitory responses. Primary and secondary outcome measures will be assessed at baseline, 1-day, 1-month, and 3-months post-intervention.

**Discussion:**

As aggression is frequently observed in individuals with addictive behaviors and is closely linked to deficits in regulatory behaviour, the intervention, if proven efficacious, could offer a cost-effective and time-efficient alternative to traditional cognitive-behavioral and anger management interventions. Conversely, should the intervention prove ineffective, the findings would indicate that this may not be a potential area for further exploration in this population.

**Trial registration:**

The study protocol was registered prospectively with the Clinical Trials Registry of India (CTRI) on August 07, 2024 (Registration Number: CTRI/2024/08/072033) (URL: https://ctri.nic.in/Clinicaltrials/rmaindet.php?trialid=113292&EncHid=61291.44954&modid=1&compid=19).

**Supplementary Information:**

The online version contains supplementary material available at 10.1186/s13063-026-09503-y.

## Introduction

### Background and rationale {9a}

The dual process model of addiction explains it as a syndrome of dysregulated motivation, with a parallel interplay of dominating automatic, impulse-driven behaviours and deteriorating cognitive regulatory processes [1, 2]. In line with this theoretical proposition, research has targeted implicit mechanisms for reducing the extent to which individuals engage with their addictive tendencies. Impulse-driven behaviors have been targeted by attentional bias modification [3], approach-avoidance training [4], and interpretation bias training [5]. And the reverse has also been attempted with interventions targeting deficits in regulatory behaviors such as inhibitory control [18].

Empirical research has supported the notion that impairments in inhibitory control contribute to addictive behaviors and have been linked with both substance use disorders and gambling behaviour [6, 7]. However, this lack of inhibitory control may not stay confined to addiction. It may also extend to and impact other psychological domains that depend on the same regulatory mechanisms, such as aggression [8, 9]. Aggression is also frequently reported among individuals with substance use and gambling problems [10–12], lending further support to this link. Together, these findings point to a cycle where impaired inhibitory control, aggression, and addictive behaviors interact in a loop of cause and consequence (see Fig. 1).

**Fig. 1 Fig1:**
[figure not shown]
Interplay of inhibitory control, addiction, and aggressive behaviours

This hypothesis is also in line with the problem behaviour theory [13] which proposes that gambling, substance use, and violent behaviours commonly co-occur in a ‘complex multi-condition behavioural syndrome’; creating a non-isolated, interrelated pattern of maladaptive behaviour. This has also been supported by subsequent empirical research [12–16].

The behaviour of individuals with low inhibitory control is often dominated by impulsive precursors such as unconscious patterns and automatic behaviour, which tend to bypass deliberate cognitive processing [17]. These individuals may react reflexively to internal urges and external stimuli especially under stressful conditions without adequately considering the consequences of their actions, leading to maladaptive responses. Such responses can vary depending on personal vulnerabilities and contextual factors. Common manifestations include aggression, continuing or relapsing into addictive behaviours, or engagement in other forms of risky decision-making [17].

In the field of addiction, this has led researchers to employ Inhibitory Control Training (ICT) to target these deficits through computerized behavioural interventions in an attempt to effectively reduce the frequency of substance consumption in participants [18–20]. Around 16 studies have explored this form of treatment all over the world by utilizing the go/no go paradigm or the stop signal paradigm in addressing substance use disorders. Building upon this approach, similar paradigms have been applied in the context of gambling behaviour, with Verbruggen et al. [21] and Verbruggen et al. [22] investigating the effects of proactive motor control training on gambling behavior. These approaches focus on strengthening inhibitory control via the association of no-go or stop cues and addiction-related stimuli. However, the results have been inconclusive and with mixed findings so far, possibly due to methodological heterogeneity across studies. Some of these studies have used sham training as a comparator where stimuli are presented in a way that prevents any form of association.

The application of ICT has not yet been extended to other psychological domains that are also influenced by deficits in inhibitory control. Since impaired inhibitory control can contribute to the inability to regulate aggression, which is strongly prevalent in people with substance use disorders and gambling behaviour; employing ICT could potentially address aggressive behaviors in this target population. Addressing this gap, the current research seeks to assess the effectiveness of ICT in decreasing aggressive behaviours and enhancing behavioural regulation among persons with substance use and gambling disorders. By extending the use of ICT beyond addiction-related outcomes, this research can contribute to understanding its utility as a transdiagnostic intervention, which can potentially be used in managing co-occurring maladaptive behaviours.

Aggression has been classically treated using cognitive-behavioral approaches and anger management training. Although effective, these treatments are usually time-consuming and require specialized training. In contrast, Inhibitory Control Training can be a time-efficient intervention, working on inhibitory control through underlying unconscious processes, to reduce aggressive tendencies. Such cognitive modification interventions have not yet been tested much among the Indian population. This research will mark the first implementation of ICT in an attempt to manage aggression among patients with co-occurring substance use disorder and gambling behaviour in the Indian setting.

### Explanation for the choice of comparator {9b}

ST will be matched with active training in terms of both stimulus exposure and response requirements, but will have the contingency agreement reduced to 50%, thereby preventing the formation of associations between aggressive stimuli and inhibitory responses. Similar studies in the past have used sham training as a comparator where stimuli were presented in a way that prevents any form of association [20, 23, 24]. Some other studies working with a different population have also shown the same [25]. Another reason for the inclusion of sham training in the control group is that while controlling for time and attention, it might provide information into the underlying mechanism of functioning of this intervention—differential effects between the groups, if observed, can be attributed to the formation of implicit inhibitory associations.

### Objectives {10}

The primary objective of this study will be to evaluate the efficacy of Inhibitory Control Training (ICT) in reducing overt aggressive behaviours among individuals with co-occurring substance use disorder and gambling behaviour. Additionally, the study aims to assess whether reductions in aggression and improvements in inhibitory control will be associated with subsequent changes in substance use patterns and gambling behaviour over follow-up periods.

## Methods: patient and public involvement, and trial design

### Patient and public involvement {11}

Patients and members of the public will not be directly involved in the reporting of this trial. However, the development and validation of the intervention employed in this randomized controlled trial will be informed by the target population. Patient feedback obtained during routine clinical interactions at the study site will be used to refine task instructions, session duration, and the overall feasibility of implementation. In addition, participant input will be incorporated during the pre-testing and cognitive interviewing stages to be undertaken as part of the translation of the study questionnaires.

### Trial design {12}

The research study will utilize a two-group, parallel, superiority randomized controlled trial (RCT) design. The primary objective of the trial is to determine whether inhibitory control training produces a greater reduction in aggressive behaviour compared to sham training, thereby testing the superiority of the experimental intervention over the comparator. Although the trial is designed as a superiority study, some aspects of it may be exploratory in nature due to our interest in whether the intervention works and how it works. Eligible participants will be randomly allocated in a 1:1 ratio to either the experimental group or the control group. In the experimental group, participants will receive inhibitory control training, while those in the control group will receive a sham version of the training. Both groups will also be receiving treatment as usual (TAU), as decided by the clinical team. Evaluation will occur at four time points: Pre-intervention (baselines), post-intervention at 1-Day post ICT, 1-month post ICT (± 4 Days), and 3-months post ICT (± 7 Days). The trial is designed to evaluate the superiority of Inhibitory Control Training over sham training in reducing aggressive behaviours.

## Methods: participants, interventions and outcomes

### Trial setting {13}

The participants will be recruited from the In-Patient Department (IPD) of the National Drug Dependence Treatment Centre (NDDTC), All India Institute of Medical Sciences (AIIMS), New Delhi.

### Characteristics of the people who are needed for the trial

**Table Taba:** 

Characteristic	The people we would expect to see included
Age	Adult participants aged 18 years and above; age will be recorded in years and summarised using mean and standard deviation
Sex	Only male participants will be included in the study
Gender	No other gender identities will be included or reported in this study other than males
Race, Ethnicity and Ancestry	Not specifically collected or categorised; participants are recruited from the Indian population
Socioeconomic Status	Participants will not be included or excluded based on their socioeconomic backgrounds; however, socioeconomic details will be recorded using Modified Kuppuswamy Socioeconomic Scale (2023)
Geographic Location	Participants will be recruited from a tertiary care inpatient facility in Ghaziabad, Haryana, India. No eligibility criteria will be applied based on place of birth, duration of residence, or rural–urban background; however, these details will be recorded for descriptive purposes
Other Characteristics Relevant to the Trial	Adult male inpatients diagnosed with substance use disorder and exhibiting problem or pathological gambling behaviour; participants must be clinically stable, able to provide informed consent, and capable of engaging in brief computer-based behavioural training

### Eligibility criteria for participants {14a}

Male patients aged 18 years or older meeting the criteria for problem (Score ≥ 1) or pathological (Score ≥ 5) gambling on the South Oaks Gambling Screen (SOGS) [26], diagnosed with substance use disorder as per DSM-5 [27] criteria, and willing to give informed consent will be considered for inclusion in this study. Exclusion criteria include the presence of severe medical or psychiatric conditions that could interfere with participation, and a lifetime history of neurological illness, neurodevelopmental disorders, or traumatic head injury, as per the available clinical history.

The study has an inclusion criterion of male participants only because the inpatient population at the study site comprises a very small proportion of female patients. Including a highly unequal number of female participants would not allow for meaningful subgroup analyses and could introduce additional variability, thereby limiting the interpretability of the findings.

Participants will be recruited from an inpatient setting to ensure the feasibility of the intervention delivery. The training protocol requires two sessions per day over three consecutive days, due to which availability of participants across extended daytime hours will be necessary. Conducting the intervention in an outpatient setting might have led to logistical challenges. The inpatient setting was therefore decided upon to allow for feasible delivery of the intervention and minimized disruptions related to scheduling.

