### Outcomes {16}

#### Study instruments for primary outcomes

The Overt Aggression Scale‐Modified [29, 30] is a semi-structured interview designed to evaluate various categories of aggressive behaviors. Four sub-components make up the overall aggression (AGG) score: Verbal Aggression, Aggression Against Object, Aggression Against Others, and Aggression Against Self. Subcomponent scores are determined by multiplying the number and severity level of aggressive behaviors of each type during the prior week. Additional scores include a Global Anger and Aggression (GAA) score composed of two item ratings: Subjective experience of anger and overt expression of anger. The OAS‐M has been shown to be reliable and valid, with good psychometric properties in terms of internal consistency, inter-rater reliability, test–retest reliability, face validity, convergent validity, divergent validity, and discriminant validity [30]. The primary outcome of the study will be the change in overall aggression score from baseline to the 1-Month post-intervention follow-up, as measured using the Overt Aggression Scale–Modified (OAS-M), and will be summarized using mean values and standard deviations.

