#### Participant timeline {18}

Patients admitted to the National Drug Dependence Treatment Centre (NDDTC) will be administered upon a brief screening process. The screening will initiate only when the participant is able to actively engage in the study, ensuring they are not intoxicated or in a state of withdrawal. Withdrawal charting will be done using the Clinical Institute Withdrawal Assessment of Alcohol Scale, Revised (CIWA – Ar) [40] for alcohol, Clinical Opiate Withdrawal Scale (COWS) [41] for opioids, Minnesota Nicotine Withdrawal Scale (MNWS) [42], the Cannabis Withdrawal Scale (CWS) [43] for cannabis, and the Clinical Institute Withdrawal Assessment Benzodiazepines (CIWA—B) [44] scale for Benzodiazepines. If the participant is found intoxicated or experiencing withdrawal, the screening process will be paused. It will be resumed only after a reassessment of withdrawal symptoms has been conducted within the next 24–48 h.

Patients diagnosed with substance use disorder by a psychiatrist will then undergo the South Oaks Gambling Screen (SOGS) for the identification of problem or pathological gambling in the patients. Once it is ascertained that the participant fulfills the inclusion/exclusion criteria, written consent will be taken by the primary investigator, and patients will be randomized to either the experimental or control group. The Alcohol, Smoking, and Substance Involvement Screening Test (WHO-ASSIST Version 3.0) and the Overt Aggression Scale – Modified (OAS – M) will be administered along with the sociodemographic and clinical proformas. Other baseline assessments, including the Stimulus Evaluation Task, Inhibitory Control Task, and the Timeline Follow-Back Scale (TLFB) will also be performed post randomization. All questionnaires and assessments will be administered by verbally posing the questions (and options) to the patients. The demographic details, medical/psychiatric history of the participant, their family history, and treatment record will also be recorded (see Supplementary File 2).

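### Entry does not require any aggression, while the primary outcome is a fall in a score with a floor at 0; many zero scorers at baseline would make a null result ambiguous

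*Protocol article*

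**What the plan says.** **Objective.** Objectives {10} sets out to "evaluate the efficacy of Inhibitory Control Training (ICT) in reducing overt aggressive behaviours among individuals with co-occurring substance use disorder and gambling behaviour". Trial design {12} frames this as superiority: a larger reduction than under sham training.

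**Entry.** Eligibility criteria {14a} admits "Male patients aged 18 years or older meeting the criteria for problem (Score ≥ 1) or pathological (Score ≥ 5) gambling", as scored by the SOGS. The inclusion list then ends with a diagnosis and consent, for patients "diagnosed with substance use disorder as per DSM-5 [27] criteria, and willing to give informed consent will be considered for inclusion in this study". The exclusions concern severe medical or psychiatric conditions, neurological illness, neurodevelopmental disorder and head injury. The table of participant characteristics describes "Adult male inpatients diagnosed with substance use disorder and exhibiting problem or pathological gambling behaviour" and adds clinical stability, capacity to consent and ability to do the task. Neither place mentions aggression, past or present.

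**Outcome.** Under Outcomes {16}: "The primary outcome of the study will be the change in overall aggression score from baseline to the 1-Month post-intervention follow-up", measured with the OAS-M. On scoring: "Subcomponent scores are determined by multiplying the number and severity level of aggressive behaviors of each type during the prior week".

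**Order of events.** Participant timeline {18} says that once the criteria are met, "written consent will be taken by the primary investigator, and patients will be randomized to either the experimental or control group". The OAS-M is described after that step, and the remaining baseline assessments are said to be done after randomisation as well.

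**Blinding.** Under {24a} only participants are blinded; one investigator enrols, delivers the training, assesses and analyses.

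**Reading of a null.** The Abstract and the Discussion both say that an ineffective result would indicate that this is not an area worth exploring further.

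**The concern.** The population is not selected for the problem that the trial aims to reduce. A settled inpatient with no aggressive act in the past week is eligible and enters the primary analysis at the lowest possible score. Timing makes this more likely: screening waits until the patient is neither intoxicated nor in withdrawal, so part of the one-week OAS-M window may be spent on the ward.

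The main risk is to interpretation. If many participants start at 0, a null could mean that there was little to reduce rather than that the training does not work. The protocol commits in advance to the second reading. Because the baseline OAS-M is described after allocation, with an assessor who knows the arm, the later division of participants into zero and non-zero scorers is also not protected from knowledge of allocation.

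**Working it through.** **1. The plan's own figures.** Sample size {19} uses a cited pre-post change from 3.44 (SD 3.89) to 1.07 (SD 1.92) with correlation 0.5.

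- Effect size: 2.37 / √(3.89² + 1.92² − 2 × 0.5 × 3.89 × 1.92) = 2.37 / 3.369 = 0.703. The stated 0.70 is reproduced.
- Attrition: 26 / (1 − 0.60) = 65 per group, 130 in total. Reproduced.
- The 26 itself arises from a one-sided two-sample t-test at d = 0.70 (25.94). The paired test that the section names would give 19 two-sided or 15 one-sided. That is a separate matter and is not pursued here.

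**2. The floor.** The score is number times severity of acts in the prior week. No act gives 0, and the change from 0 cannot be negative. For such a patient the arms can differ only in how often, or how far, he rises above 0 by 1 month.

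**3. How many zeros?** The protocol gives no figure. As an illustration only, take a negative binomial with the cited baseline moments (mean 3.44, variance 3.89² = 15.13):

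- k = 3.44² / (15.13 − 3.44) = 1.01
- P(0) = (1.01 / (1.01 + 3.44))^1.01 ≈ 0.22

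The OAS-M score is a product of count and severity, not a pure count, so this shows only that zeros are plausible when the SD exceeds the mean on a score bounded at 0.

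**4. What zeros would do to power.** Assumptions: a share q scores 0 at baseline and shows no between-arm effect; the SD is unchanged; 36 per arm are seen at 1 month (65 × 0.55 = 35.75, from the 45% one-month dropout in Sample size {19}); two-sided alpha is 0.05; two-sample t-test. With d = 0.70 the power is 83%. Two readings of 0.70 are possible:

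- *Reading A:* 0.70 is the effect in patients above 0 only. Then d = 0.70 × (1 − q).
- *Reading B:* 0.70 is the average over a cited sample with about 22% zeros. The effect above 0 is then 0.70 / 0.777 = 0.90, and d = 0.90 × (1 − q).

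| Share at 0 | A: d | A: power | B: d | B: power |
|---|---|---|---|---|
| 20% | 0.56 | 65% | 0.72 | 85% |
| 30% | 0.49 | 54% | 0.63 | 75% |
| 40% | 0.42 | 42% | 0.54 | 62% |
| 50% | 0.35 | 31% | 0.45 | 47% |

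Under B, a share of about 22% gives d = 0.70 again, so nothing is lost against plan. Only an excess over the cited sample costs power.

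**5. Sensitivity to the SD.** If zero scorers also add no variance, the loss is smaller. Under A, with 26 per group and a one-sided test (80% without dilution), power for 20% to 50% zeros is 70%, 64%, 58% and 51%, against 64%, 54%, 44% and 35% with the SD held.

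**The case against.** **The population is deliberate.** The objective names people with substance use disorder and gambling behaviour, not aggressive patients, and the Background argues that aggression is frequent in this group. This stands: the text does not contradict itself, and an entry threshold is a choice about whom to study. But frequent is not universal, and no expected baseline OAS-M distribution is given for this site.

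**Zero scorers are not uninformative.** A reader might infer that they cannot show any effect. The documents do not support that. The contrast is between arms, the score covers one week, baseline is taken in stabilised inpatients, and follow-up comes after discharge. A patient at 0 can rise, and if this happens less under training he contributes. Nor does one week at 0 show that he lacks the problem.

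**The power loss is not documented.** A reader might take the column for reading A as the cost. It treats 0.70 as the effect in aggressive patients, although 0.70 comes from the whole cited sample, zeros included if there were any. Moreover, 0.70 is a pre-post effect, and Sample size {19} itself warns that sham may work comparably, so even the 83% is not an established between-arm power. This stands: the table shows direction and sensitivity, not an estimate.

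**A subgroup must not carry the conclusion.** One might wish to rest the efficacy claim on participants above 0 at baseline. That would displace the intention-to-treat analysis in {27b} with a smaller group that an unblinded assessor may have classified after allocation. This also stands, and it limits the remedy.

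**Conclusion.** The concern holds in a limited form. As written, entry requires no aggression, the primary outcome is change in a prior-week score with a floor at 0, and the OAS-M cannot act as a screen because it is described after randomisation. Patients at 0 cannot show a reduction and can inform the contrast only through prevented worsening. With many of them, the effect is diluted and a null is ambiguous, which the Abstract and Discussion do not allow for.

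The loss of power is an unquantified risk. It is little or none if the share of zeros is near that in the cited sample, and larger if the share is higher; at 50% zeros the illustration gives 47% or 31%, depending on what 0.70 already contains. These figures rest on an assumed share, an assumed distribution and a borrowed pre-post effect. They do not show that the trial is underpowered for this reason.

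**What to change.** 1. Administer and score the OAS-M after consent but before the envelope is opened.
2. Keep the all-randomised intention-to-treat comparison as primary. Report the share scoring 0 at baseline by arm. Prespecify a supportive 1-month between-arm analysis in participants with a baseline score of at least 1, and state that for patients already enrolled the baseline may have been scored after allocation.
3. Amend the Abstract and Discussion so that a null is not read as evidence of inefficacy if many participants had no aggression at baseline.

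An entry threshold for the remaining enrolment, due to end in December 2026, is optional for the sponsor to consider. It narrows the population, slows recruitment and mixes two entry rules within one trial.

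The cost of items 1 to 3 is a reordered assessment, a short amendment and one extra analysis with fewer patients. No new instrument is needed.
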